## Abstract

**Background:**

Post hepatectomy liver failure (PHLF) remains a significant risk in patients undergoing curative liver resection for cancer, however currently available PHLF risk prediction investigations are not sufficiently accurate.

The Hepatectomy risk assessment with functional magnetic resonance imaging trial (HEPARIM) aims to establish if quantitative MRI biomarkers of liver function & perfusion can be used to more accurately predict PHLF risk and FLR function, measured against indocyanine green (ICG) liver function test.

**Methods:**

HEPARIM is an observational cohort study recruiting patients undergoing liver resection of 2 segments or more, prior to surgery patients will have both Dynamic Gadoxetate-enhanced (DGE) liver MRI and ICG testing.

Day one post op ICG testing is repeated and R15 compared to the Gadoxetate Clearance (GC) of the future liver remnant (FLR-GC) as measure by preoperative DGE- MRI which is the primary outcome, and preoperative ICG R15 compared to GC of whole liver (WL-GC) as a secondary outcome.

Data will be collected from medical records, biochemistry, pathology and radiology reports and used in a multi-variate analysis to the value of functional MRI and derive multivariant prediction models for future validation.

**Discussion:**

If successful, this test will potentially provide an efficient means to quantitatively assess FLR function and PHLF risk enabling surgeons to push boundaries of liver surgery further while maintaining safe practice and thereby offering chance of cure to patients who would previously been deemed inoperable. MRI has the added benefit of already being part of the routine diagnostic pathway and as such would have limited additional burden on patients time or cost to health care systems. (*Hepatectomy Risk Assessment With Functional Magnetic Resonance Imaging - Full Text View -*
*ClinicalTrials.gov*, n.d.)

**Trial registration:**

ClinicalTrials.gov, ClinicalTrials.gov NCT04705194 - Registered 12th January 2021 – Retrospectively registered

**Supplementary Information:**

The online version contains supplementary material available at 10.1186/s12885-021-08830-4.

## Background

The liver is the most common site of metastases in patients with colorectal cancer (CRC). Up to two thirds of CRC patients go on to develop liver metastasis during the course of their disease and 18% actually presents with liver metastasis at their first consultation [1–3].. Primary liver cancers are the fifth most commonly occurring cancer in men and the ninth in women worldwide with 840,000 new cases diagnosed in 2018 alone [4]. This includes mainly two types of cancer: hepatocellular carcinomas (HCC), often associated with chronic liver disease and cholangiocarcinomas (CCA), tumours of the biliary tree that most commonly occur in the perihilar region of the liver, but also within the liver parenchyma and as a result require extensive resections.

Whilst several treatment modalities exist the only curative option for these patients is surgical resection ranging from minor parenchymal preserving metastasectomy to major liver resection removing up to 75% of the liver. The latter group is technically challenging and associated with significant risks and complications; potentially the most serious of these being post-hepatectomy liver failure or PHLF [5] which can ultimately result in death. PHLF occurs in 5–10% of patients undergoing major hepatectomy due to inability of the remnant liver to maintain its synthetic, excretory, and detoxifying functions and not regenerate at a sufficient pace. PHLF ranges in severity from transient hepatic insufficiency while the liver regenerates to full-blown fulminant hepatic failure [6–8]. The latter group is associated with a high risk of mortality of up to 54% [9].

Preoperative methods used to reduce such risk include portal vein embolisation (PVE) of the part of the liver to be removed in future surgery. PVE will result in diverting blood flow to the contralateral side and subsequent hypertrophy of the liver remnant (May and Madoff 2012). A second alternative is to perform the operation over two stages which often involves clearing of tumour(s) on one side and ligating the portal vein branch to other side at first stage followed by second stage after several weeks to remove the part of liver that has atrophied. Alternatively, a similar outcome can be achieved via an open surgical procedure called ALPPS (associating liver partition and portal vein ligation in staged hepatectomy). ALPPS involves two operations that are spaced in a shorter time interval. All of these techniques are associated with increased complications of different magnitude. PVE, the least invasive carries risk of some morbidity and failure to induce hypertrophy in a proportion of patients. The two stage operations have increased morbidity of two operations and ALPPS is associated with a significant increase in mortality. The risk is high enough for ALPPS with tumours like Choilangiocarcinoma at liver hilum that it is currently contraindicated for these tumours. The risk of failure to induce hypertrophy persists with two stage hepatectomy whereas ALPPS, despite the significantly increased complications has a higher chance of succeeding in inducing hypertrophy.

Selection of patients for surgery, precise planning of surgery and assessing the need for interventions to induce liver hypertrophy would benefit greatly from an accurate prediction of the function of future liver remnant (FLR) and assessment of risk of PHLF. Unfortunately, reliable and reproducible tests to predict function of remnant liver are currently not available in clinical practice. This results in either patients being turned down for potentially curative treatment or patients undergoing multiple interventions with additional risks including mortality when such interventions are not essential due to adequate function of remnant liver. Quantitative liver function tests such as indocyanine green (ICG), LiMAX (maximum liver function capacity) assess the liver as whole rather than the function of different parts of liver. Conventional cross sectional imaging like magnetic resonance imaging (MRI) and computerized tomography (CT) can provide an estimate of the volume of the future remnant, but this is inadequate in predicting the function in the presence of background liver disease like fibrosis, chemotherapy related injury, cirrhosis and cholestatsis. A potential solution is to combine whole liver function tests with FLR volume as determined on imaging ([10]; Y [11].; Yukihiro [12]), but this is based on an assumption that liver function is uniformly distributed across all liver segments. Hepatobiliary scintigraphy accounts for this factor [13–15], but is not widely available and is limited by inaccurate assessment of volume.

MRI-based liver function tests based on uptake of the liver-specific contrast agent Gadoxetate offer a promising approach for assessment of FLR function in clinical practice [16]. Apart from wide availability, a major advantage of Gadoxetate as compared to ICG and tracers used in hepatobiliary scintigraphy is the low extraction fraction even in healthy liver. With a fast dynamic acquisition and a pharmacokinetic analysis of the data (dynamic Gadoxetate-enhanced MRI or DGE-MRI), this enables a separate quantification of liver perfusion and hepatocellular function, as well as structural parameters such as the extracellular volume fraction [17]. Previous studies on Gadoxetate MRI for liver surgery planning use descriptive or approximate measures of Gadoxetate uptake and therefore do not fully exploit the potential offered by this extra quantitative information [18–20]. Moreover, previous work tends to focus on HCC, but inhomogeneous liver function can be relevant even in patients with liver metastases due to the effects of chemotherapy-induced liver injury and obesity-associated liver disease [21].

A pilot study with DGE-MRI in 29 patients with colorectal liver metastases (CRLM), using post-operative bilirubin as a surrogate for liver function, suggested that DGE-MRI biomarkers significantly improved the predictions of post-operative function compared to biochemical markers and volumetric assessment of the FLR [22]. A parameter of particular interest was the normalised Gadoxetate clearance (GC), a combination of perfusion and function that determines the rate at which the liver clears Gadoxetate from the blood pool. GC has units of mL/min/kg and measures the volume of plasma (mL) fully cleared of Gadoxetate per minute and per kg body weight. Potentially, the GC of the FLR (FLR-GC) can offer a clear and widely available cut-off value to determine if a surgery is safe to perform, irrespective of the underlying disease or the body size of the patient considered for surgery.

The primary aim of HEPARIM is to determine if DGE-MRI biomarkers of liver function and perfusion offer a significant improvement in the prediction of post-hepatectomy liver function. ICG clearance will be used as a reference measurement of post-operative liver function and correlated against DGE-MRI before surgery. As a secondary aim, DGE-MRI will be validated directly by performing ICG pre-operatively at the same time as the MRI and correlating the ICG clearance with whole-liver GC (WL-GC). A positive result on the primary aim can potentially improve the safety profile of hepatic surgery and open the door to extend the indication to wider groups of patients and avoid harmful interventions where they are not required.

## Methods/design

### Objectives and outcome measures

#### Primary objective

To determine if DGE-MRI can improve predictions of post-hepatectomy liver function. The primary outcome measure is the correlation between preoperative FLR-GC (mL/min/kg) and ICG R15 1 day after surgery (%).

#### Secondary objectives

To validate DGE-MRI based measurements of liver function against a gold-standard liver function test. The outcome measure is the correlation between preoperative WL-GC (mL/min/kg) and a simultaneously measured ICG R15 (%).To determine the relationship between volumetric and functional liver growth after PVE/ALPPS. Outcome measure is the correlation between growth in FLR volume and growth in FLR-GC after the first stage.To determine if preoperative DGE-MRI can improve predictions of PHLF (any grade) over and above routinely available data. HEPARIM will adopt the PHLF definition by the International Study Group of Liver Surgery (ISGLS).To determine if preoperative DGE-MRI can improve predictions of 90-day post-operative outcome over and above routinely available data. (*Hepatectomy Risk Assessment With Functional Magnetic Resonance Imaging - Full Text View -*
*ClinicalTrials.gov*, n.d.)

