#### Data analysis

A univariable analysis will be performed comparing preoperative MR predictions of post-operative liver function against post-operative ICG-R15 (primary objective) and comparing preoperative MR measures of whole liver function against preoperative ICG-R15 (secondary objective). Second the correlations will be investigated in a multivariable analysis to determine if MRI adds value to existing preoperative biomarkers for predicting PHLF and 90-day outcome. Multivariate models will be derived for predicting both outcomes and it will then be tested whether this combined score is statistically significantly worse when DGE-MRI is removed from the prediction. In the PVE/ALPPS group, changes in volume will be correlated with changes in function of the FLR between pre PVE/pre-ALPPS and post-PVE/post-ALPPS.

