### Sample size considerations

#### Audit

Sample size calculation was informed by an audit of the preceding year. Between October 2016 and October 2017, a total of 165 patients who met the inclusion criteria underwent surgery at St James’s hospital. 15% of these patients underwent PVE. Patients undergoing major liver resection had a rate of PHLF equal to 9%, although the rate of those requiring medical intervention as a result of their PHLF was only 3.6%. Of the eligible patients, 67% had an MRI in Leeds after the MDT, and for a further 7% the MDT requested a local MRI.

For practical and funding reasons the maximum duration of patient recruitment in HEPARIM was set at 2 years. Based on experience in a pilot study [22], a 50% recruitment rate was assumed in patients that do not require an additional MRI visit for research purposes. A 25% recruitment rate was assumed in primary surgery patients that need an additional MRI, and in PVE/ALPPS patients.

With these assumptions the maximum number of participants over the 2 years is 134, including 122 into the primary surgery arm and 12 into the PVE/ALPPS arm. The pilot study also demonstrated that 18% of patients recruited into the study ultimately did not undergo surgery. Hence only 82% of the 122 recruited patients in the surgery arm will feed into the primary objective, or a total of 112 including those in the PVE/ALPPS arm.

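### Growth in FLR-GC appears to contain growth in FLR volume, so the planned PVE/ALPPS correlation is expected to be positive anyway and does not show whether function grows in proportion to volume

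*Protocol article*

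**What the plan says.** The second item under Secondary objectives sets the aim, "To determine the relationship between volumetric and functional liver growth after PVE/ALPPS", and names one measure for it: "Outcome measure is the correlation between growth in FLR volume and growth in FLR-GC after the first stage". The Data analysis section repeats this for the PVE/ALPPS group: "changes in volume will be correlated with changes in function of the FLR", comparing the state before with the state after PVE or ALPPS. Neither place names a slope, a ratio or a per-volume measure of function.

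The Background defines the quantity: "GC has units of mL/min/kg and measures the volume of plasma (mL) fully cleared of Gadoxetate per minute and per kg body weight". It then considers FLR-GC as a possible threshold for safe surgery: "Potentially, the GC of the FLR (FLR-GC) can offer a clear and widely available cut-off value to determine if a surgery is safe to perform". The Primary objective gives FLR-GC the same unit, mL/min/kg. No formula for FLR-GC is printed, and the source of the FLR volume is not stated.

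On numbers, the Audit section expects 134 participants, "including 122 into the primary surgery arm and 12 into the PVE/ALPPS arm".

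**The concern.** A clearance per kg of body weight is not divided by the amount of liver that does the clearing. If the remnant grows and each mL works as before, FLR-GC rises with it. The two quantities to be correlated are then a part (volume growth) and a whole that contains it (volume growth combined with change in function per mL). Two difficulties follow.

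- **The reference value is not zero.** A clearly positive r is expected even if per-mL function changes independently of volume growth. Reading it as evidence that function per mL follows volume would be a mistake.
- **Correlation ignores level and scale.** If function lags behind volume by the same factor in every patient, r does not change.

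This matters because the Background argues that remnant volume is an inadequate guide to function when the background liver is diseased. Separating function from volume is the study's rationale, and r alone does not separate them.

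**Working it through.** **1. The plan's own numbers.** The article gives no sample size or expected correlation for this outcome, so the relevant figure is the size of the PVE/ALPPS arm. The inputs from the Audit section are 165 eligible patients a year for 2 years, 15% PVE, 67% + 7% = 74% needing no extra MRI visit, and recruitment rates of 50% and 25%.
- PVE/ALPPS arm: 330 × 0.15 × 0.25 = 12.4
- Primary surgery arm: 280.5 × (0.74 × 0.50 + 0.26 × 0.25) = 122.0
- Total: 134.4

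The stated 12, 122 and 134 are reproduced.

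**2. Structure of FLR-GC.** Let V be FLR volume, c clearance per mL of liver and W body weight. The unit and the proposed use as a whole-remnant threshold imply FLR-GC = V × c / W. This formula is inferred, not quoted. At stable weight:

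fold-change in FLR-GC = fold-change in V × fold-change in c.

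**3. Expected r when per-mL change is unrelated to volume growth.** Assume volume growth gV with mean 0.35 and SD 0.20, and an independent per-mL change gF with mean 0 and SD s. FLR-GC growth is (1 + gV)(1 + gF) − 1.
- Covariance with gV: 0.20² = 0.04
- Variance of FLR-GC growth: (1.35² + 0.04)(1 + s²) − 1.35² = 0.04 + 1.8625 s²
- So r = 0.20 / √(0.04 + 1.8625 s²)

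| s | r | r² |
|---|---|---|
| 0.10 | 0.83 | 0.68 |
| 0.20 | 0.59 | 0.35 |
| 0.30 | 0.44 | 0.19 |

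The log scale gives the same picture without assuming a mean. With k = SD(change in log c) / SD(change in log V), r = 1/√(1 + k²), which is 0.89, 0.71 and 0.45 for k = 0.5, 1 and 2.

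**4. A uniform lag.** Multiply every patient's FLR-GC fold-change by 0.8. Mean FLR-GC growth falls from 35% to 0.8 × 1.35 − 1 = 8%, while volume growth stays at 35%. This is a linear transformation of one variable, so r is exactly what it was.

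**5. Per-mL function that falls as volume grows.** Assume change in log c = −0.5 × change in log V + error (SD 0.1), with an SD of 0.2 for change in log V. Change in log FLR-GC is then 0.5 × change in log V + error. The planned r is 0.1/√(0.1² + 0.1²) = +0.71, while the correlation of volume growth with per-mL change is −0.71. In simulated samples of 12 the averages were +0.69 and −0.69. If the coefficient is −1 instead of −0.5, the planned r is 0, so a low r does carry information.

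**6. Precision at n = 12.** For an observed r of 0.6, Fisher's z is 0.693 and the half-width is 1.96/√9 = 0.653. The limits are tanh(0.040) = 0.04 and tanh(1.346) = 0.87.

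For a mean log-ratio with an assumed SD of 0.1 to 0.3, the half-width is 2.201 × SD/√12, or 0.06 to 0.19 log units. The ratio is then known to within a factor of about 1.07 to 1.21.

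**The case against.** The strongest reply is that the coupling is largely genuine. A larger remnant really does clear more, and how closely volume growth tracks growth in total function is a fair question, because volume is what conventional imaging supplies. On this reading r is a legitimate descriptive measure. It falls from 0.83 to 0.44 as per-mL variability rises, so it responds to something real. This stands, and it is why r should be kept.

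Some stronger readings are tempting, but the documents do not support them.

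- **That the correlation is uninformative or mostly artefact.** A low or negative r would be informative. The built-in share (r²) runs from 0.68 down to 0.19 on the assumptions used, so it is not large throughout.
- **That a false-positive test is planned.** The article says only that the changes will be correlated. It states no test of r = 0.
- **That the outcome misses a stated question about timing of surgery.** The objective asks for the relationship between the two kinds of growth. The interval before surgery appears only in the Discussion, as a possible later use.
- **That the 18% who do not reach surgery should be deducted from the 12.** Under Study procedures (PVE/ALPPS arm), the second research visit comes before the final decision on surgery, and data from patients who then do not proceed are kept for the secondary objectives. The Audit section also leaves the 12 undiminished: 0.82 × 122 + 12 = 112.

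Two limits remain. The product formula is an inference, and the volume source is unknown. Taking volume from the routine CT would remove segmentation error shared with the MRI, but not the structural link.

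**Conclusion.** The point holds in a limited form. FLR-GC as described very probably scales with FLR volume. The single stated outcome is therefore expected to be positive without any link between volume growth and function per mL, and it cannot by itself show whether function grows in proportion to volume. The size, 0.83 to 0.44, rests on assumed growth figures; the direction does not, provided that FLR-GC is a whole-remnant clearance and body weight is stable between visits. Blindness to a uniform lag or change of scale is a property of correlation and needs no assumption.

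This concerns one secondary outcome in about 12 patients and leaves the primary objective untouched. The small number limits any analysis of this objective, including the addition proposed here. It is a worthwhile improvement and not a fault that undermines the study.

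**What to change.** Keep the correlation as a descriptive measure, and say that it is not to be read against zero because FLR volume is a component of FLR-GC. Beside it, add for each patient:

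ratio = (FLR-GC after / FLR-GC before) ÷ (FLR volume after / FLR volume before).

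At stable body weight this is the fold-change in clearance per mL of FLR. If weight has changed, first multiply FLR-GC by body weight at each visit. Report the mean of the log-ratio with its 95% CI against 0 (equivalently, the back-transformed ratio against 1), and show the individual values. Describe both results as exploratory. State how FLR-GC is computed from the images and which scan supplies the FLR volume, so that readers can judge the coupling.

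The cost is a few lines of analysis. No new scans, measurements or patients are needed.

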### Study design

#### Summary

HEPARIM is an observational cohort study that will aim to recruit 134 patients referred locally for a one- or two-stage liver resection of 2 segments or more. Participants will undergo a preoperative ICG liver function test and a DGE-MRI scan of the liver, and another ICG test at 1 day after surgery. Additional pre- and postoperative data will be collected from their medical records including demographics, routine imaging, biochemistry, pathology and radiology reports, any data collected in the 90-day follow-up visit. Participants who will undergo a staged resection with either PVE or ALLPS will have additional DCE-MRI and ICG tests before the first stage.

#### Study authorizations

The HEPARIM study has been approved by the North West - Liverpool Central Research Ethics Committee (IRAS project ID: IRAS 240787, REC reference: 19/NW/0139). The study sponsor is University of Leeds.

#### Setting

A single high-volume tertiary referral hepatobiliary surgery center in the United Kingdom (Leeds Teaching Hospitals Trust).

#### Timing

Recruitment was scheduled to occur over a two-year period which began on 1st July 2019. The timing has been significantly disrupted due to the ongoing COVID-19 pandemic, ongoing at the time of writing. Patients will be followed up for a three-month period post-operatively. Recruitment will end when the target number of patients have been recruited and have completed their imaging, surgery and follow up, or when the research team feel that continuing the study is either unsafe or unfeasible.

#### Data analysis

A univariable analysis will be performed comparing preoperative MR predictions of post-operative liver function against post-operative ICG-R15 (primary objective) and comparing preoperative MR measures of whole liver function against preoperative ICG-R15 (secondary objective). Second the correlations will be investigated in a multivariable analysis to determine if MRI adds value to existing preoperative biomarkers for predicting PHLF and 90-day outcome. Multivariate models will be derived for predicting both outcomes and it will then be tested whether this combined score is statistically significantly worse when DGE-MRI is removed from the prediction. In the PVE/ALPPS group, changes in volume will be correlated with changes in function of the FLR between pre PVE/pre-ALPPS and post-PVE/post-ALPPS.

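### The primary objective claims improved prediction of post-operative liver function, but its only assigned analysis is a univariable correlation with no comparator

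*Protocol article*

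**What the plan says.** The end of the Background states the primary aim as finding out whether "DGE-MRI biomarkers of liver function and perfusion offer a significant improvement in the prediction of post-hepatectomy liver function". The Primary objective section repeats the comparative wording: "To determine if DGE-MRI can improve predictions of post-hepatectomy liver function". It then defines the measure: "The primary outcome measure is the correlation between preoperative FLR-GC (mL/min/kg) and ICG R15 1 day after surgery".

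The Data analysis section assigns the method: "A univariable analysis will be performed comparing preoperative MR predictions of post-operative liver function against post-operative ICG-R15 (primary objective"). The same section then plans a multivariable analysis "to determine if MRI adds value to existing preoperative biomarkers for predicting PHLF and 90-day outcome". Models are to be derived for those two outcomes, and "it will then be tested whether this combined score is statistically significantly worse when DGE-MRI is removed from the prediction".

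Under Secondary objectives, the PHLF and 90-day objectives each name routinely available data as the benchmark. The primary objective names no benchmark.

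**The concern.** Improvement is a comparative claim: it needs a prediction without MRI to set against one with it. A correlation between one marker and the outcome shows association only.

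The gap matters here because the Background gives reasons to expect an association even if MRI contributes nothing new. It describes an existing approach: "A potential solution is to combine whole liver function tests with FLR volume as determined on imaging". It adds that this approach assumes function is spread evenly over the liver. If that assumption held, FLR-GC would be roughly whole-liver function times remnant share. It would still track day-1 ICG while telling the surgeon nothing beyond the older approach. The planned primary analysis cannot separate that case from one in which regional MRI information helps.

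At stake is the primary conclusion. The Background links a positive primary result to safer surgery and wider indications, and that inference needs evidence of gain over current prediction.

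**Working it through.** **1. The plan's own figures**

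Inputs from the Audit section: 165 eligible patients a year, two years, 15% PVE, 67% + 7% = 74% needing no extra MRI visit, recruitment of 50% (no extra MRI) or 25% (extra MRI, or PVE/ALPPS), and 18% not reaching surgery.

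- Eligible: 2 × 165 = 330.
- PVE/ALPPS: 330 × 0.15 × 0.25 = 12.4.
- Primary surgery: 280.5 × (0.74 × 0.50 + 0.26 × 0.25) = 122.0.
- Total: 134.4 (stated 134).
- Contributing to the primary objective: 0.82 × 122 + 12 = 112.0 (stated 112).

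The Power calculation gives a 95% interval of 9.12 to 10.88 for the slope of ICG-C on FLR-GC. Assuming a log-SD of 1.0 for FLR-GC (none is given), error variance proportional to FLR-GC, and n = 120, simulation gives 9.13 to 10.89. The figure is reproducible under that assumption, but it concerns only the single-marker slope. It says nothing about gain over other predictors.

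**2. Which outcome gets which analysis**

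| Outcome | Status | Analysis assigned | Comparison with and without MRI |
|---|---|---|---|
| Day-1 ICG R15 | Primary | Univariable correlation | No |
| PHLF | Secondary | Multivariable | Yes |
| 90-day outcome | Secondary | Multivariable | Yes |

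The PHLF analysis cannot stand in for the missing cell. It is a different outcome, and at the audit rate of 9% it would have about 0.09 × 112 = 10 events.

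**3. How large the correlation can be with zero added value**

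All correlations and SDs below, and the two-sided 5% level, are assumptions.

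*One routine predictor, n = 112.* If FLR-GC is unrelated to R15 given the routine predictor, then |r(FLR-GC, R15)| = |r(FLR-GC, routine)| × |r(routine, R15)|. Chance of significance by Fisher z: Φ(atanh|r| × √(n − 3) − 1.96).

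- 0.8 × 0.7 = 0.56: 100%.
- 0.7 × 0.6 = 0.42: 99.7%.
- 0.6 × 0.5 = 0.30: 90%.
- Weaker links give less: 0.5 × 0.5 = 0.25, 76%.

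In 20,000 simulated trials for each of the first three cases, adding FLR-GC to the routine predictor was significant in 5%, the nominal rate. The mean gain in R-squared was 0.005 to 0.007.

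*Whole-liver function plus volume, n = 110, log scale.* Assumed log-SDs: 0.30 for function, 0.35 for volume, 0.25 for MRI noise, 0.40 for outcome noise. The outcome is modelled as a clearance, so the sign reverses for R15.

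- Shared variance: 0.30² + 0.35² = 0.2125.
- FLR-GC variance: 0.2125 + 0.25² = 0.275.
- Outcome variance: 0.2125 + 0.40² = 0.3725.
- |r| = 0.2125 / √(0.275 × 0.3725) = 0.66, significant in 100% of simulated trials.

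**4. Power of an added-value test at the planned size**

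Fisher z with three covariates: Φ(atanh(partial r) × √(n − 6) − 1.96).

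| Partial r | n = 110 | n = 95 |
|---|---|---|
| 0.20 | 54% | 48% |
| 0.25 | 74% | 67% |
| 0.30 | 88% | 83% |

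The n = 95 column is an assumed loss of day-1 ICG measurements.

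**The case against.** The strongest reply has five parts.

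- **The article may simply be condensed, with detail left to an analysis plan.** This does not stand. The article itself fixes both the outcome measure and the analysis for the primary objective, and they do not answer the objective as worded.
- **Added value is tested.** This is true for PHLF and 90-day outcome, with a stated benchmark. A reader might infer that the trial never tests added value at all, and the document does not support that. The gap is confined to post-operative function. The sentence introducing the multivariable work refers loosely to investigating the correlations, but it limits its purpose to the two secondary outcomes.
- **No success rule is stated.** This stands. The article gives no alpha, null hypothesis or threshold for the correlation, and the sample size rests on slope precision. A reader might infer that the trial would automatically declare success. The text does not say so, and the significance rates above are illustrative. The Discussion also promises only hypotheses for later trials.
- **Pre-operative ICG is not a fair mandatory benchmark.** This stands. A reader might infer that DGE-MRI must beat pre-operative ICG combined with FLR volume. However, the study-procedures and blinding sections treat ICG as a research addition. The document's own benchmarks are routinely available data (Secondary objectives) and, in the pilot, biochemistry and FLR volumetry (Background).
- **A nested test is not automatically clean.** This stands. The 5% rejection rate assumes baseline predictors measured without error. In the function-plus-volume model, giving pre-operative ICG a log-scale error SD of 0.10, 0.15 or 0.20 (assumed) raised rejection to about 14%, 34% and 60% in 20,000 simulated trials each, with no regional information in the MRI. FLR-GC then gains credit as a second noisy reading of the same function.

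**Conclusion.** The point holds. The stated primary objective is improvement, the assigned primary analysis measures association, and no planned analysis compares prediction of post-operative function with and without DGE-MRI. Followed as written, the plan cannot support its primary claim, although it can support a claim that FLR-GC is associated with day-1 ICG R15.

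This conclusion follows from the wording and needs no simulation. The size is illustrative: with no added value and n of about 110, |r| of roughly 0.30 to 0.66 and significance in roughly 90% to 100% of trials, under the assumed inputs and two-sided 5% level.

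**What to change.** Choose one of two routes before analysis.

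1. **Test the claim.** Keep the correlation as a reported result. Extend the planned comparison with and without DGE-MRI to day-1 ICG: a pre-specified model on routinely available data and FLR volume, fitted with and without FLR-GC. Report the gain in R-squared or the partial correlation with a 95% confidence interval. Add a sensitivity model that includes pre-operative ICG, and state that measurement error in ICG or volume can make FLR-GC appear to add value. Restate the sample size justification for this quantity.
2. **Match the claim to the analysis.** Reword the primary objective and the planned conclusion as association or validation of FLR-GC against post-operative ICG R15.

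Route 1 costs one more model and some wording. Routine data and pre-operative ICG are already planned, and FLR volume should be obtainable from the scan that yields FLR-GC. Its downside is a stricter criterion with only moderate power for small gains. Power falls further if day-1 tests are missing, since they are done only where feasible and patients with an ICG contraindication found at screening stay in the study. Route 2 costs only wording but gives up the improvement claim for post-operative function.
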